## Abstract

**Background:**

The Korean National Cancer Screening Program has been providing annual fecal immunochemical test for colorectal cancer (CRC) to adults aged 50 years and older since 2004. The Korean Colonoscopy Screening Pilot Study was developed to evaluate the effectiveness of colonoscopy screening for CRC incidence and mortality, screening-related complications, and acceptability of colonoscopy as a primary modality for the national CRC screening program.

**Methods:**

This study and its protocols have been approved by the Korean Public Institutional Review Board and the National Cancer Center Institutional Review Board. We obtain written informed consent from all participants. The target population is males and females aged 50–74 years living within the pilot sites. A total of 26,640 participants will be recruited for colonoscopy screening. Subjects who have been diagnosed with CRC, who are currently undergoing treatment for CRC, or who have undergone colonoscopy screening within the past 5 years are not allowed to participate. All participants need to complete baseline questionnaires. This pilot study is currently conducted by 104 endoscopists from 57 national cancer screening institutions (42 primary, 10 secondary, and 5 tertiary institutions) located in Goyang-si, Gimpo-si, and Paju-si. The number of endoscopists, medical institutions, and districts participating in the pilot study will be expanded, if necessary. Participating endoscopists at each medical institution perform colonoscopy and report the colonoscopy results to a centralized electronic case report system. We conduct a telephone survey after 7 days and 4 weeks post-colonoscopy to assess for procedure-related complications and satisfaction of the participants. In case of abnormal findings from colonoscopy screening, we track the results from follow-up diagnostic tests. Data from this pilot study will be linked to the diagnostic workup results, the Korean Cancer Registry, and death certificate data for analysis of the performance, long-term effects, and cost-effectiveness of colonoscopy.

**Discussion:**

The results will provide critical information to determine whether the introduction of colonoscopy as the primary modality of the Korean National Cancer Screening Program would be acceptable and feasible.

*Trial registration* Korean Clinical Research Information Service registry, KCT0004142. Registered on 15 July 2019, http://cris.nih.go.kr/cris/en/search/search_result_st01.jsp?seq=16227

## Background

Colorectal cancer (CRC) was responsible for more than 10% of the global cancer burden in 2018 [1]. It is the third most common cancer in men and the second most common cancer in women worldwide, with more than 730,000 new cases being diagnosed each year [2]. CRC has a high burden of disease in Korea as well as the second most common cancer and the third most common cause of cancer-related deaths in men and women combined [3].

CRC starts as a locally confined polypoid precursor lesion and has a long preclinical stage, with most symptoms presented at an advanced stage. Morbidity and mortality of CRC can be significantly reduced if the disease is diagnosed and treated at an earlier stage [4, 5]. Therefore, screening for CRC before the development of symptoms may be beneficial for improved long-term outcomes. There are several screening modalities for CRC, which include fecal occult blood test (FOBT), sigmoidoscopy, colonoscopy, computed tomography colonography, and stool or blood DNA test. Colonoscopy allows for the detection and removal of early cancer and precancerous adenoma in one-step, and thus, it may have a large effect on decreasing CRC incidence and mortality.

Since 2004 as part of the National Cancer Screening Program (NCSP), the government of the Republic of Korea has been providing annual fecal immunochemical test (FIT) for free to adults aged 50 years and older as the primary modality for detecting CRC. Individuals with a positive FIT result are then referred for either colonoscopy or double-contrast barium enema, which are both provided free-of-charge. However, 68.7% of the patients preferred colonoscopy as the primary method for CRC screening [6]. There has been consistent demand for the introduction of colonoscopy as the primary method for the national CRC screening program. However, colonoscopy is an invasive and expensive procedure. In addition, it entails a risk of complications, requires extensive bowel preparation, and is difficult to learn. Therefore, the benefits and harms of colonoscopy should be carefully evaluated. Currently, we lack population-based clinical trials investigating both the magnitude of effectiveness and the harms of colonoscopy screening for CRC.

For these reasons, the Korean Ministry of Health and Welfare commissioned the Korean Colonoscopy Screening Pilot Study (K-cospi) to the National Cancer Center in January 2019 to evaluate the appropriateness and effectiveness of colonoscopy as the primary method for organized CRC screening at the population level. Accordingly, a Center for K-cospi was established in the National Cancer Center in April 2019 to develop and implement the pilot study protocol, execute the budget, facilitate the participation of eligible participants, provide ongoing support to the participating medical institutions, collect data, and evaluate the outcomes.

The Expert Advisory Committee composed of multidisciplinary experts from various fields of CRC screening, including gastroenterology, surgery, pathology, epidemiology, and preventive medicine, who are representatives from medical colleges, professional societies, or primary medical care was established to provide advice on the design and implementation of the pilot study, monitor the overall process, and ensure quality assurance of the study. In addition, the Monitoring Committee, composed of experts in either cancer screening or colonoscopy, was established to regularly monitor the operating procedures, outcomes, and safety of the pilot study.

### Aim

The primary objective of this study is to evaluate the effectiveness of colonoscopy screening for CRC incidence and mortality in the Republic of Korea. The secondary objectives of this study are to evaluate the complications related to colonoscopy screening and to assess the acceptability of colonoscopy for CRC screening.

## Methods

### Study design and setting

This is a multicenter, community-based clinical trial to evaluate the effectiveness, harms, and acceptability of colonoscopy screening for CRC. The criteria for the selection of pilot sites includedSufficient number of the target population;Epidemiologic characteristics of CRC, which represent the Korean population;Mixture of urban and rural characteristics to minimize the impact of specific regional characteristics on the study results;Even distribution of medical institutions capable of colonoscopy screening;Enough endoscopists and endoscopy units to be involved in the pilot study;Support and cooperation from local governments for the promotion and implementation of the pilot program.

Goyang-si, Gimpo-si, and Paju-si in Korea satisfied the above criteria and were selected as the pilot sites (Paju-si was additionally included in January 2020).

Medical institutions located in the pilot sites and designated as CRC screening units by the National Health Insurance Service were allowed to participate in the pilot study. They were designated as CRC screening units after undergoing a verification process to ensure that they met the application qualification and were equipped with the necessary manpower, facilities, and equipment. The verified institutions will be frequently checked for the management of equipment and facilities, in accordance with the Framework Act on Health Examination.

The essential prerequisites for endoscopists to participate in the pilot study were as follows:Employed at the medical institutions participating in the pilot study;Certified for endoscopy from either of the Korean Society of Gastrointestinal Endoscopy, the Korean Society of Digestive Endoscopy, or the Korean Society of Coloproctology, based on the time of attending an academic conference or training education and the number of endoscopies performed;Performed more than 300 colonoscopies within the last 2 years.

The Center for K-cospi prepared an information session to provide the prospective participating medical institutions with a general introduction to the pilot study, participation requirements, and application process. At the beginning of the Pilot study, a total of 36 medical institutions (26 primary, 6 secondary, and 4 tertiary institutions) located in Goyang-si and Gimpo-si were selected to participate in the pilot study with 70 endoscopists, who met the requirements. The number of pilot sites, medical institutions, and endoscopists participating in the pilot study have been gradually expanded. As of November 2020, a total of 57 medical institutions (42 primary, 10 secondary, and 5 tertiary institutions) located in Goyang-si, Gimpo-si, and Paju-si with 104 endoscopists are participating in the pilot study.

### Outcome measures

The primary outcomes for colonoscopy effectiveness are (1) the rate of detection of CRC and (2) the stage-shift effect of the colonoscopy procedure. The secondary outcomes are (1) major complications due to colonoscopy and (2) participant satisfaction and attitude towards colonoscopy screening.

### Sample size calculation

A calculated target sample size of 26,640 participants will be required to detect significant differences in the rates of cancer detection between FIT and colonoscopy. This is based on an estimated cancer detection rate of 1.2 per 1000 screened with FIT and 2.2 per 1000 screened with colonoscopy.

### Participant recruitment

Posters and leaflets have been placed in each participating medical institution, main bus and subway stops, and at public health centers within the pilot sites to raise awareness of the pilot study. In addition, the pilot study has been introduced to local newspapers of the pilot sites.

Potential participants are identified from the participating medical institutions during their visits and invited to participate if eligible. In addition, those who express interest in participating in the pilot study to the Center for K-cospia re guided to the nearest participating medical institution after eligibility screening. Table 1 lists the inclusion and exclusion criteria.

**Table 1 Tab1:** Eligibility criteria

Inclusion criteria	Exclusion criteria
Males and females aged 50–74 years	Subjects who have been diagnosed with CRC or are currently undergoing treatment for CRC
Subjects who live within the pilot sites	Subjects underwent colonoscopy screening within the last 5 years

Subjects are allowed to participate in the pilot study only once. Recruitment was initiated in August 2019 and will continue until the planned sample size is reached.

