### Screening procedures and follow-up processes

The screening procedure is described in Fig. 1. Table 2 shows the SPIRIT schedule of enrolment, interventions, and assessment of this study protocol. At the participating medical institutions, bowel preparation medication is given to participants and a colonoscopy screening date is scheduled. All participants need to complete baseline questionnaires on demographics, current physical symptoms, past medical/surgical history, family history, CRC screening history, medication, and life style before colonoscopy screening.

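### Eligibility allows people with bowel symptoms or a recent positive FIT to enrol, and gender and age matching does not remove that difference from the FIT-versus-colonoscopy comparison

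*Protocol article*

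**What the plan says.** Table 1 of the protocol article (Participant recruitment) has two inclusion criteria, "Males and females aged 50–74 years" and residence in the pilot sites. It has two exclusions: "Subjects who have been diagnosed with CRC or are currently undergoing treatment for CRC", and a screening colonoscopy in the last 5 years. The abstract gives the same set. Neither current bowel symptoms nor a recent positive FIT appears in either place.

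On recruitment, the article says: "Potential participants are identified from the participating medical institutions during their visits and invited to participate if eligible". It also uses posters and leaflets at institutions, transport stops and public health centres, local newspapers, and self-referral to the study centre.

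The relevant history is collected: "All participants need to complete baseline questionnaires on demographics, current physical symptoms, past medical/surgical history, family history, CRC screening history". The data analysis plan also links participants to the national screening programme database. The article gives symptoms and prior FIT no role in eligibility or in the comparison.

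The primary outcomes are CRC detection rate and stage shift. The sample size is described as "required to detect significant differences in the rates of cancer detection between FIT and colonoscopy", from an "estimated cancer detection rate of 1.2 per 1000 screened with FIT and 2.2 per 1000 screened with colonoscopy". The Discussion says the answer to non-randomisation is to match on gender and age with national programme data.

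**The concern.** The Background presents screening as something done before symptoms develop, and the study is meant to inform a national screening programme. As stated, the eligibility rules do not hold participants to that. A person attending with bowel symptoms, or one whose FIT has just come back positive, meets every criterion. Such people have a higher expected CRC yield than routine FIT attendees of the same gender and age, so the matching leaves the difference in place.

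The prior-FIT case is the sharper one. A cancer already flagged by FIT could be counted as a colonoscopy detection in a comparison with FIT itself.

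The planned contrast rests on few events, so a modest number of such cases matters. Stage shift is exposed too. The Background says most CRC symptoms appear at an advanced stage, so symptomatic entrants could move the colonoscopy stage mix towards later disease. For stage, the bias need not favour colonoscopy.

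**Working it through.** **1. The plan's own figure.** Inputs from Sample size calculation: FIT 1.2 per 1000, colonoscopy 2.2 per 1000, target 26,640. Alpha, power and allocation are not stated, so two-sided 5%, 80% and 1:1 are assumed here.

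n per group = [1.960 × √(2 × 0.0017 × 0.9983) + 0.842 × √(0.0012 × 0.9988 + 0.0022 × 0.9978)]² / 0.001² = 26,640.

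This matches the stated target exactly. The arithmetic is not at fault, and there is no allowance for losses.

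**2. Events behind the contrast.** 26,640 × 0.0022 = 58.6 cancers, and 26,640 × 0.0012 = 32.0. The planned gap is about 27 cancers.

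**3. Effect of higher-risk entrants on the colonoscopy rate.** Let s be the share of participants with symptoms or a recent positive FIT, and r their yield per 1000. The documents give neither; both are assumptions. With a screening yield of 2.2 in everyone else:

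observed rate = (1 − s) × 2.2 + s × r, so added rate = s × (r − 2.2) per 1000.

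| Share s | r = 10 | r = 20 | r = 30 |
|---|---|---|---|
| 2% | 0.16 | 0.36 | 0.56 |
| 5% | 0.39 | 0.89 | 1.39 |
| 10% | 0.78 | 1.78 | 2.78 |

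The range is 0.16 to 2.8 per 1000, about 17-fold. The planned difference of 1.0 is reached in 3 of the 9 cells. At r = 10 it is never reached within this range. At r = 20 it needs s = 1.0/17.8 = 5.6%, and at r = 30 it needs s = 1.0/27.8 = 3.6%.

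**4. Effect if colonoscopy screening truly detected no more than FIT.** Set the screening yield to 1.2. The share that alone would produce a rate of 2.2 is s = 1.0/(r − 1.2): 11.4% at r = 10, 5.3% at r = 20 and 3.5% at r = 30.

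The chance of a significant result favouring colonoscopy with 26,640 per group (nominal 2.5%) is:

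- s = 2%, r = 10: observed 0.98 × 1.2 + 0.02 × 10 = 1.38 per 1000, chance 8%.
- s = 2%, r = 30: observed 1.78 per 1000, chance 41%.
- s = 5%, r = 20: observed 2.14 per 1000, chance 76%.

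**The case against.** The strongest reply is that permission is not occurrence. A reader might infer that the study will enrol diagnostic cases and will overstate yield. The documents do not support that, because they show only that such people may enter, not how many do. The Background says people with a positive FIT already have free colonoscopy or barium enema, which gives them less reason to enrol. Recruitment is not confined to clinic visits, and nothing in the text shows that posters attract symptomatic people. The institutions are designated CRC screening units, so a visit need not be for bowel complaints. All of this stands and limits the likely size.

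A reader might also infer that a small enriched fraction is enough to create the whole planned difference. That holds only for the higher assumed shares and yields, and neither has a source in the documents.

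On symptoms, nothing says that national FIT attendees are free of them. The bias in the comparison is therefore less certain than the bias in the absolute yield. No symptom data are described for the comparators, so restricting only the colonoscopy side would be asymmetric and could understate colonoscopy's advantage. This stands too, and it rules out an asymptomatic-only primary set.

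Finally, analysis sets are often defined in a full protocol or analysis plan, and neither is shown here; nor is the flow chart. That is fair for analysis detail. It does not answer the point on eligibility, which the article states in full, or the stated remedy of gender and age matching, which does not address pre-test risk.

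**Conclusion.** The point holds as a possibility that the stated design leaves open. People with bowel symptoms or a recent positive FIT are eligible, and gender and age matching does not remove the resulting difference in pre-test risk. Cancers that were symptomatic or FIT-triggered can therefore enter the colonoscopy detection rate and stage distribution.

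The size cannot be derived from the documents. The 0.16-2.8 per 1000 range rests wholly on the assumed shares and yields, and it exceeds the planned 1.0 only in its upper part. The evidence is firmer for a prior positive FIT, where the same rule can be applied to both sides, than for symptoms, where the comparator's status is unknown. It would go too far to say that the detection rate will be inflated, or that the planned sample size is wrong.

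**What to change.** - In the primary FIT-versus-colonoscopy comparison of detection rate and stage, exclude participants with a positive FIT in the 12 months before enrolment. Identify them from the baseline questionnaire and the planned national programme linkage.
- Apply the same prior-FIT rule to the comparators, over the 12 months before their index FIT.
- Report the all-enrolled result alongside.
- Prespecify, as a sensitivity analysis, colonoscopy detection rate and stage in participants reporting no bowel symptoms at baseline. State which questionnaire items count as bowel symptoms. Do not make this the primary set.

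This needs wording only. The questionnaire and linkage are already planned, and recruitment and care do not change.

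The cost is a small loss of participants from the primary comparison. The target has no margin if the comparator is 1:1. Approximating power as Φ(2.802 × √(share kept) − 1.960), it falls from 80% to about 79% if 2% are lost from each group, 78% if 5% are lost and 76% if 10% are lost. A larger comparator pool would offset this: with ten FIT comparators per participant, power at 26,640 colonoscopies is about 97%.

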Currently, there are four on-going large-scale randomized controlled trials that compare colonoscopy with no screening or fecal immunochemical testing for CRC incidence or mortality in 10–15 years [17]. The trials were launched between 2009 and 2014, and the results of these trials will presumably be presented in 10 years. Therefore, findings from the present pilot study regarding the suitability of colonoscopy as the primary method for CRC screening in organized population-based screening programs are necessary to provide critical insights into the future direction of national CRC screening program in the Republic of Korea.

The protocol of this pilot study has some limitations that should be noted. First, we will not randomizing participants into the two study arms. It is difficult to carry out a randomized controlled trial because FIT is provided free-of-charge every year through the Korean NCSP. To overcome this shortcoming in the study design, the participants will be matched according to their gender and age with the data from the Korean NCSP for CRC to compare the performances of FIT and colonoscopy. Second, the generalizability of the study findings will be limited because the participation rate in this pilot study, the characteristics of participants, and the clinical setting of medical institutions may vary depending on regional characteristics. To minimize this limitation, we selected pilot sites that represent the CRC epidemiology of the whole country and have a balanced characteristic of urban and rural areas. In addition, we evenly included first, second, and tertiary hospitals so that the study can be conducted under real-world circumstances.

In summary, the findings of this pilot study will provide critical information regarding the acceptability and feasibility of colonoscopy as the primary modality of the Korean National Cancer Screening Program. They will lead to more effective and efficient screening programs for CRC.

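### Matching on gender and age cannot control self-selection by lasting colorectal cancer risk in the colonoscopy versus FIT comparison of detection rates

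*Protocol article*

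**What the plan says.** The Background of the protocol article gives the purpose as evaluating colonoscopy "as the primary method for organized CRC screening at the population level". It describes the existing FIT programme as free to everyone from age 50 and names no exclusion based on risk.

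Under Participant recruitment, "Table 1 lists the inclusion and exclusion criteria". Inclusion requires residence in the pilot sites and is open to "Males and females aged 50–74 years". The two exclusions are "Subjects who have been diagnosed with CRC or are currently undergoing treatment for CRC" and "Subjects underwent colonoscopy screening within the last 5 years". On the route into the study, the same section says: "Potential participants are identified from the participating medical institutions during their visits and invited to participate if eligible". Posters, leaflets and local newspapers bring in further people, who contact the study centre themselves.

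Outcome measures makes the cancer detection rate and the stage shift the primary outcomes. The Discussion acknowledges that there is no randomisation and gives the countermeasure: "the participants will be matched according to their gender and age with the data from the Korean NCSP". Gender and age are the only matching variables named.

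Before the procedure every participant completes a questionnaire that covers, among other items, "past medical/surgical history, family history, CRC screening history, medication, and life style before colonoscopy screening". The Data analysis plan section gives these items no role in the comparison with FIT.

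**The concern.** Everyone in the colonoscopy group chose to have a colonoscopy. The comparator consists of people who used the stool test in the national programme. Someone who knows of affected relatives, long-standing bowel disease or a hereditary syndrome may be readier to volunteer for colonoscopy than to take a stool test. If so, the two groups differ in underlying cancer risk at the same age and gender, and the detection rate depends directly on that risk.

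The excess would then be read as a benefit of the test, when part of it comes from who volunteered. The colonoscopy yield and the difference from FIT would be too high, the stage comparison would rest on groups of different risk, and the planned cost-effectiveness analysis would inherit the error.

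**Working it through.** **Inputs from the documents.** Detection rates of 1.2 per 1000 (FIT) and 2.2 per 1000 (colonoscopy), and a target of 26,640, all from Sample size calculation.

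**Reproducing the plan's figure.** The section states no error rates. Assume a two-sided 5% level, 80% power, equal groups and the usual pooled-variance formula, with p1 = 0.0012, p2 = 0.0022 and mean 0.0017:

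n = [1.960 × √(2 × 0.0017 × 0.9983) + 0.842 × √(0.0012 × 0.9988 + 0.0022 × 0.9978)]² / 0.0010² = 26,640 per group.

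This agrees exactly. So 26,640 is the colonoscopy group, and the FIT group is taken below to be the same size.

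**Expected cancers.** 26,640 × 0.0022 = 58.6 with colonoscopy and 26,640 × 0.0012 = 32.0 with FIT.

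**Effect of over-representation.** Let f be the extra share of high-risk people beyond the mix found among FIT users, and RR their detection rate relative to that mix. The documents give neither, so both are assumptions. The colonoscopy rate becomes 2.2 × [1 + f(RR − 1)] per 1000. The FIT rate stays at 1.2.

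| f | RR | Rate per 1000 | Extra cancers | Difference per 1000 |
|---|---|---|---|---|
| 0 | any | 2.200 | 0 | 1.00 |
| 1% | 3 | 2.244 | 1.2 | 1.04 |
| 2% | 5 | 2.376 | 4.7 | 1.18 |
| 5% | 3 | 2.420 | 5.9 | 1.22 |
| 10% | 5 | 3.080 | 23.4 | 1.88 |

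For example, with f = 5% and RR = 3: 2.2 × 1.10 = 2.42, and 26,640 × 0.00022 = 5.9.

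**What would explain the whole planned difference.** f = 1.0 / [2.2 × (RR − 1)], which is 45% at RR 2, 23% at RR 3 and 11% at RR 5.

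**The opposite error.** Suppose 5% of both groups are at high risk, with 3 times the detection rate of the rest. There is then no bias in the all-participant comparison. Removing these people from the colonoscopy group alone gives 2.2 / (1 + 0.05 × 2) = 2.00 per 1000. The difference from all FIT users becomes 0.80 instead of 1.00, which is too low.

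**The case against.** A reader might infer that Table 1 is itself wrong, because a population question should not admit people at known high risk. The documents do not support this. The programme as described has no risk-based exclusion, so the programme and its FIT records will contain such people too. Broad eligibility mirrors that population.

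A reader might also picture recruitment through specialist gastroenterology clinics. The article speaks only of visits to participating institutions, 42 of 57 of which are primary, and of public advertising. It also reports that 68.7% preferred colonoscopy, so wanting it does not mark out high-risk people. That they volunteer more readily is plausible but not shown.

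Two further points reduce the weight of the concern. The 5-year exclusion may remove some high-risk people who were examined recently, although its wording covers screening colonoscopy only. And up to the 5% at 3-fold scenario, the extra 5.9 cancers are below one Poisson standard deviation of the expected count (√58.6 = 7.7). This second point does not dispose of the matter, because the bias acts in one direction and a confidence interval does not reflect it.

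Finally, an unseen analysis plan may contain further adjustment, and the absence of a sensitivity table from an article is no fault in itself. What stands is what the article does state: it offers matching on gender and age as the way to overcome non-randomisation. The second limitation in its Discussion concerns regional generalisability and does not cover self-selection by risk.

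**Conclusion.** The point holds as a limit on the comparison with FIT. It is not a fault in eligibility. Matching on gender and age cannot control self-selection by lasting colorectal cancer risk, and if high-risk people are over-represented among participants relative to FIT users, the detection rate and the difference are biased upward.

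The size cannot be known from the documents. For an assumed excess of 1% to 5% at 3-fold risk the difference is 1.04 to 1.22 per 1000 instead of 1.00. With equal prevalence the bias is near zero. A large effect needs strong assumptions, such as a 10% excess at 5-fold risk. The required sample size does not change as long as 2.2 per 1000 is the rate without such an excess. The direction and size of any effect on stage mix cannot be derived from the figures given. This is a minor point, worth settling because the needed data are already collected.

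**What to change.** Leave Table 1 and the all-participant primary analysis unchanged. Add to the Data analysis plan section:

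- A flag derived from the baseline questionnaire for family history of colorectal cancer, inflammatory bowel disease and hereditary syndrome, defined before the comparison with FIT is run.
- A sensitivity analysis giving the detection rate and stage mix with and without flagged participants.
- The same flag applied to FIT records where the linked data allow. Where they do not, a statement that, as regards this flag, the difference between unflagged colonoscopy participants and all FIT users is conservative (biased downward).
- A commitment to qualify the conclusion about population screening if the results with and without flagged participants differ.

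The unflagged group should not become the sole basis for the population conclusion, because the programme also serves the people it leaves out.

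The cost is one derived variable and one extra table, with a smaller denominator in the sensitivity analysis. Flag data may be incomplete on the FIT side, and the report should say so.
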